## Programme summary

|                      |                                                                                                                                                                                                                                                                                                                                                                                                                                                                                                                                                                                                                                                                                                                                                                                                                                                                                       |
|----------------------|---------------------------------------------------------------------------------------------------------------------------------------------------------------------------------------------------------------------------------------------------------------------------------------------------------------------------------------------------------------------------------------------------------------------------------------------------------------------------------------------------------------------------------------------------------------------------------------------------------------------------------------------------------------------------------------------------------------------------------------------------------------------------------------------------------------------------------------------------------------------------------------|
| Name of study        | Preoperative cognitive training for reduction of delirium in patients recovering from coronary artery bypass grafting (CT-LIFE): a multicenter, single-blinded, randomized trial                                                                                                                                                                                                                                                                                                                                                                                                                                                                                                                                                                                                                                                                                                      |
| Purpose of study     | To evaluate the effectiveness of preoperative cognitive training in reducing postoperative delirium incidence among patients undergoing coronary artery bypass grafting.                                                                                                                                                                                                                                                                                                                                                                                                                                                                                                                                                                                                                                                                                                              |
| Research Design      | Prospective, multicenter, large sample, randomized controlled study design                                                                                                                                                                                                                                                                                                                                                                                                                                                                                                                                                                                                                                                                                                                                                                                                            |
| Research population  | Adults aged $\geq 18$ years who were scheduled for elective coronary artery bypass grafting with general anaesthesia                                                                                                                                                                                                                                                                                                                                                                                                                                                                                                                                                                                                                                                                                                                                                                  |
| Selection criteria   | 
 
(1) Sign the informed consent;
 
(2) Patients who plan to undergo isolated coronary artery bypass grafting with general anaesthesia;
 
(3) Adults aged <math>\geq 18</math> years;
 
(4) Enrolled participants at least 10 days prior to their surgical procedure.
 
                                                                                                                                                                                                                                                                                                                                                                                                                                                                                                                                             |
| Exclusion criteria   | 
 
(1) Patients who had a life expectancy <math>< 6</math> months;
 
(2) A history of psychiatric or neurological disorders (including depression, severe central nervous system depression, schizophrenia, epilepsy, and Parkinson's or Alzheimer's disease);
 
(3) Significant impairments such as blindness, severe deafness, or dementia that might hinder cognitive testing;
 
(4) Prior use of psychotropic or opioid medications, a previous history of delirium before surgery;
 
(5) A documented history of alcohol abuse or withdrawal within the past six months;
 
(6) Inability to communicate effectively before surgery due to coma or dementia;
 
(7) Ongoing participation in another clinical trial;
 
(8) Planned re-operation within seven days of the first.
 
 |
| Research Groups      | 
 
(1) Cognitive training group
 
(2) Routine care group
 
                                                                                                                                                                                                                                                                                                                                                                                                                                                                                                                                                                                                                                                                                                                                                                        |
| Main indicators      | The incidence of delirium from postoperative day 1 to postoperative day 7 or before discharge, whichever occurred first.                                                                                                                                                                                                                                                                                                                                                                                                                                                                                                                                                                                                                                                                                                                                                              |
| Secondary indicators | 
 
(1) cumulative incidence of POD;
 
(2) incidence of severe delirium;
 
(3) postoperative cognitive dysfunction (POCD) on postoperative day 7 or at discharge if earlier;
 
(4) cognitive function one month after surgery;
 
(5) 30-day all-cause mortality;
 
(6) durations of intensive care unit and postoperative hospital care;
 
(7) elapsed time from the end of surgery to delirium onset;
 
                                                                                                                                                                                                                                                                                                                                                                                        |

Version number: 1.2

|                        |                                                                                                                                                                                                                                                                                                                 |
|------------------------|-----------------------------------------------------------------------------------------------------------------------------------------------------------------------------------------------------------------------------------------------------------------------------------------------------------------|
|                        | (8) duration of delirium;
(9) the total number of delirium-positive days;
(10) cognitive function at three time points;
(11) postoperative intubation time;
(12) intensive care unit readmission within 30 days after surgery.
(13) number of days alive and out of the hospital within 30 days. |
| Statistical analysis   | Comparison of incidence of delirium, characteristics of delirium,
and prognosis of patients                                                                                                                                                                                                                  |
| Expected test progress | One year                                                                                                                                                                                                                                                                                                        |

## 1. Background

Coronary artery bypass grafting (CABG) is a widely performed surgical procedure of significant importance. Despite advancements in surgical techniques, neurocognitive dysfunction remains a major concern for patients recovering from CABG. [1,2] The mechanisms through which coronary artery bypass graft (CABG) surgery impacts cognitive function include several key factors. First, changes in cerebral blood flow occur during the surgical process under cardiopulmonary bypass, where the heart is maintained in a non-beating state to transplant other vessels to the narrow or blocked areas of the coronary arteries, potentially resulting in decreased cerebral blood flow and subsequent cerebral ischemia. Second, cerebrovascular events may arise from the surgeon's manipulation of the coronary arteries or other vessels, potentially leading to the release of embolic materials and causing cerebral infarction or minor cerebrovascular events, thus affecting cognitive function. Third, ischemia/reperfusion can trigger a systemic inflammatory response, causing the release of various inflammatory mediators, impacting the nervous system and increasing the risk of embolism, ultimately leading to cognitive dysfunction. Additionally, patient age is a significant risk factor, particularly with the increasing aging population, as elderly patients undergoing CABG surgery, who often have comorbidities such as hypertension, high cholesterol, and diabetes, are at markedly higher risk of postoperative delirium, cognitive dysfunction, and other neurological and psychiatric complications. Lastly, the complexity and prolonged duration of the surgery itself may also be associated with the risk of neurological complications, particularly due to the extended periods of anesthesia and cardiac arrest, further increasing the duration of cerebral blood flow changes and the overall risk. [3-6] Postoperative delirium (POD), an acute onset, waxing and waning disturbance of consciousness hallmarked by disorganized thinking and inability to focus, sustain or shift attention that typically occurs 24-72 hours after surgery, and cannot be explained by a pre-existing dementia, occurs in 30% to 50% of CABG patients, [7-9] adversely affecting prognosis, quality of life, caregiver burden, and healthcare costs. [10-12]

Understanding the pathophysiology of POD is limited, hindering the development of targeted interventions. The factors contributing to the onset of postoperative delirium, the complexity of diagnosis, numerous complications, and the difficulty in controlling the risk of adverse drug reactions have posed significant challenges to the development and exploration of effective treatment methods. Therefore, the prevention and treatment of postoperative delirium remains a focal and pressing issue. In 2014, the American Geriatrics Society (AGS) and the American College of Surgeons (ACS) jointly released clinical practice guidelines for the prevention and treatment of postoperative delirium. [13] These guidelines, formulated according to the standards of the National Institutes of Health, suggested that no drugs have shown significant therapeutic or preventive effects on postoperative delirium, and thus, safe and effective pharmacological treatments for delirium have yet to be established. The guidelines emphasized the importance of non-pharmacological prevention strategies, medical staff education, medical assessment of delirium causes, optimization of non-opioid pain management strategies, and the avoidance of high-risk medications. Notably, non-pharmacological interventions have consistently proven to be the most effective primary prevention strategy for delirium in surgical patients during non-intensive care hospitalization. [14,15] Therefore, non-pharmacological clinical trials emerged at the beginning of the 21st century, encompassing promoting physical exercise, optimizing existing medical

conditions, or nutritional interventions to mitigate significant risk factors, such as those related to vascular health. [16,17] The most widely studied intervention for delirium in hospitalized non-surgical patients is the Hospital Elder Life Program (HELP).[17] Based on the Yale Delirium Prevention Program, the Hospital Elder Life Program (HELP) implements a standardized protocol targeting six delirium risk factors: pre-existing cognitive impairment, sleep deprivation, immobility, visual impairment, hearing impairment, and dehydration. It has been demonstrated to reduce delirium by 14.4% in medical inpatients, resulting in an estimated cost savings of more than \$1.2 million per year in a 500-bed community teaching hospital. Recently, a modified approach based on HELP, emphasizing early post-operative mobilization, nutrition, and cognitive activities, was employed with a surgical population. Among 179 elderly patients undergoing elective abdominal surgery, none experienced postoperative delirium, whereas the control group of 77 patients had an incidence of postoperative delirium of 16.7%.[15]

A series of risk and protective factors have been reported to alter the risk for cognitive decline, mild cognitive impairment or dementia, conceivably via reserve-related mechanisms. [18-23] Cognitive reserve focuses on the idea that there are individual differences in adaptability (i. e. flexibility, efficiency, capacity, compensation) of functional brain processes that allow some people to cope better than others with age-and disease-related brain change, which means cognitive reserve may help compensate for the effects of pathological changes across individual cognitive functions. Original support for the cognitive reserve concept came from epidemiologic studies, primarily in Alzheimer's disease (AD).[24] Presumably cognitive reserve accumulates most during childhood and young adulthood, but it may also build up in older age,[25] which arguably underscores the importance of intellectual engagement throughout the lifespan. A substantial body of evidence suggests that enriched environments facilitate learning and memory capabilities in both human and animal models. Animals living in environments rich in social and cognitive stimuli demonstrate enhanced learning and memory, reduced cellular responses to stress, augmented neurogenesis in the dentate gyrus, increased brain volume and weight, greater dendritic branching, and a rise in synaptic formation.[26-28] Similarly, in humans, factors such as higher education and other forms of cognitive enrichment appear to buffer against cognitive decline and the onset of dementia in older adults, as well as enhance cognitive flexibility.[29] The underlying mechanisms may be akin to those observed in animal studies.

Several studies have taken on the task of identifying ways to augment cognitive reserve. Interventions aimed at exercising cognitive functions typically involve a set of standardized tasks for guided practice, which are designed to reflect specific cognitive functions such as memory, problem solving and information processing speed (ACTIVE Trial).[30] These tasks may be presented in the form of pen-and-paper exercises or computer-based online programs. The ACTIVE trial represents the inaugural large-scale, multi-center clinical study aimed at investigating the influence of cognitive training on cognitive function and daily life capabilities of community elderly. The subsequent 10-year follow-up of the trial conclusively revealed that older adults living in the community who undertook 10 to 14 weeks of structured cognitive training exhibited notable enhancements in cognitive function and demonstrated superior maintenance of daily living activities compared to their untrained counterparts. Although these improvements gradually diminish over time, the effects of memory training endure for a minimum of 5 years, while reasoning and processing speed training maintain impact for at least 10 years. A systematic review and meta-analysis incorporating 25 randomized controlled studies indicated that cognitive exercise training may also enhance the cognitive function of patients with mild cognitive

impairment.[31] Gates et al. demonstrated that cognitive training may attenuate the cognitive decline process in high-risk individuals.[32] Moreover, another meta-analysis suggests that cognitive training leads to measurable improvements in cognitive performance in individuals with Parkinson disease (PD), particularly in working memory, executive functioning, and processing speed, which are typically impaired in the disease. [33] A recent article published in Nature indicated that video games can have lasting benefits on cognitive function after as little as 10 hours of exposure over 2 weeks.[34]

Just recently, cognitive reserve is regarded as a potentially modifiable protective factor that may guard against the development of postoperative delirium and postoperative cognitive dysfunction.[35] Despite strong evidence favoring the ability of cognitive activity (structured and unstructured) to enhance cognitive reserve, our preliminary systematic review and meta-analysis revealed a notable scarcity of studies applying cognitive activity to perioperative patients to counteract postoperative cognitive impairment, particularly in the context of cardiac surgery with postoperative delirium as the primary outcome.[36] Our meta-analysis included only a few randomized controlled trials on perioperative cognitive training, most of which were small-sample feasibility studies. The Prevention of Early Postoperative Decline trial,[37] a feasibility study of 40 patients having cardiac surgery, suggested that patients scheduled for elective cardiac surgery were more likely comply with cognitive training in the preoperative stage, compared to other stages of the perioperative period. Another in-hospital cognitive training trial with consistent supervision, along with allotted breaks to prevent stress and help consolidate learning, provided some meaningful gains in cognitive function.[38] However, this study is also merely a pilot investigation that conducted postoperative cognitive training on a cohort of 50 patients. And finally, a recent randomized trial reported that preoperative cognitive training reduced delirium by 42% in older patients recovering from major noncardiac surgery, which, however, was derived from a post hoc analysis that removed 4 patients who did not meet the minimum adherence criteria.[39] Hence, there is currently still a lack of strong evidence to demonstrate whether cognitive training can be applied to surgical patients and whether it truly can, by enhancing the preoperative cognitive reserve of patients, to some extent, counteract the adverse cognitive effects of surgery and anesthesia, ultimately reducing the risk of postoperative cognitive impairment.

## **2.Objective**

The purpose of this multicenter trial is to study the effectiveness of preoperative cognitive training in preventing postoperative delirium among patients with coronary artery bypass grafting.

### **2.1Primary Aim**

To evaluate the extent to which preoperative in-hospital cognitive training reduces delirium in patients recovering from coronary artery bypass grafting surgery.

### **2.2 Secondary Aims**

(1) To evaluate the feasibility of implementing cognitive training in the preoperative period and the compliance of patients.

- (2) To evaluate the effectiveness of preoperative cognitive training in reducing postoperative cognitive dysfunction among patients undergoing coronary artery bypass grafting.
- (3) To evaluate whether cognitive training has varying degrees of effect across patients with different baseline cognitive levels.
- (4) To evaluate the potential dose-response relationship between the total hours of cognitive training and risk of delirium.
- (5) To evaluate the effect of preoperative cognitive training on days alive out of hospital 30 (DAOH30) after surgery, 30-day all-cause mortality compared with routine care.

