### **3.4 Randomization Procedure**

Patients were assigned by computer to either cognitive training or routine care in a 1:1 ratio stratified by

study site with random blocking. The computer-generated randomization schema was developed by an unblinded statistician and allocation was concealed from study investigators in sequentially numbered sealed opaque envelopes.

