### 4.2.3 General considerations

**Data set:** The assessment of primary endpoint will be performed based on m ITT set. The per protocol set is mainly used for sensitivity analysis. Patients who engaged in cognitive training for 3 or more hours were considered to have met our minimum compliance threshold, and included in per protocol set. The establishment of this threshold is derived from the results of our preliminary meta-analysis.

**Covariates and subgroup analysis:** Subgroup analysis will be performed and the subgroup analysis will be carried out as exploratory. To evaluate treatment effect heterogeneity on the primary outcome, predefined subgroup analyses were performed based on surgical methods, age, sex, education level, and baseline cognitive function. Interactions between cognitive training and each variable were assessed by adding interaction terms to the logistic regression model.

**multi-center effect analysis:** This is a multicenter RCT study, and there may be center effects among different centers. The logistic regression models will be used to control the multi-center effect, with the different centers set as fixed effect.

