#### **General analysis:**

The data analyses mainly include statistical description and statistical inference. Quantitative data will be described by central tendency and dispersion tendency. The normally distributed data of central tendency and dispersion tendency will be described as means and standard division, respectively. The non-normally distributed data of central tendency and dispersion tendency will be described as median and quartiles. The qualitative data will be described as frequency and percentage. Statistical inference,

independent t test or non-parameter test will be used to compare the quantitative data between the two groups, while chi-square test or Fisher's exact test will be used for comparing the qualitative data between the two groups.

For missing data, imputation techniques were used. Statistical analyses were performed using SPSS 23.0 (IBM SPSS) and R (R software 4.2.1), and 2-sided  $P < 0.05$  was considered to be statistically significant in all statistical tests.

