#### **4.2.5 Analysis of other endpoints**

For secondary and exploratory endpoints, continuous data will be presented as means (SDs) or median (IQRs), as appropriate. The secondary endpoint followed no Gaussian distribution, will be presented as median (interquartile range) and tested by Mann-Whitney U test. POCD was defined as a 1 standard deviation decline in MoCA score on postoperative day 7, or at discharge if earlier, compared to baseline. This definition aligns with previous definitions of POCD and current recommendations for defining POCD or delayed neurocognitive recovery. [48,49] Mantel-Haenszel  $\chi^2$  and Cuzick tests assessed a potential dose-response relationship between the total hours of cognitive training and incidence of delirium. Analyses of delirium duration and delirium-positive days were conducted using the Zero-inflated Poisson regression model. Regarding the assessment of delirium severity, ordinal logistic regression model was used to model no delirium, delirium and severe delirium. Additionally, a post-hoc analysis incorporating study site, age, surgical technique, baseline educational level and cognitive function of the participants was conducted.

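### If site affects DAOH30, ICU or hospital stay, or intubation time, the unstratified rank test planned for them loses power, because randomisation is stratified by site

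*Protocol*

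**What the plan says.** All references are to the protocol.

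- **Aim.** Section 2.2, item 5: "To evaluate the effect of preoperative cognitive training on days alive out of hospital 30 (DAOH30) after surgery". The same item adds 30-day mortality.
- **Endpoints.** The programme summary lists "durations of intensive care unit and postoperative hospital care", intubation time and days alive and out of hospital as secondary. Section 3.7.3 bounds DAOH30 between 0 and 30 and sets it to 0 for patients who die or are still in hospital at day 30.
- **Randomisation.** Section 3.4: "Patients were assigned by computer to either cognitive training or routine care in a 1:1 ratio stratified by" "study site with random blocking".
- **Tests.** Under General analysis in 4.2.3: "independent t test or non-parameter test will be used to compare the quantitative data between the two groups". Section 4.2.5 says that a non-Gaussian secondary endpoint "will be presented as median (interquartile range) and tested by Mann-Whitney U test". Neither place names a site stratum or a site term.
- **Centre.** Section 4.2.3 accepts that centre effects may exist and answers: "The logistic regression models will be used to control the multi-center effect, with the different centers set as fixed effect".
- **Other mention of site.** Section 4.2.5 closes with a post-hoc analysis that includes study site among other variables, but names neither endpoint nor model.

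**The concern.** Blocked allocation within site keeps the arms nearly balanced at each site, so differences between sites largely cancel from the comparison of arms. A Mann-Whitney test on pooled ranks still counts those differences as noise. Its standard error is then too large for the design, the real error rate falls below 5%, and power is lost.

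The protocol sees that centres may differ, but its remedy is a model for binary outcomes. It does not reach outcomes measured in days or hours. Discharge and extubation practice could plausibly differ between hospitals, though the protocol gives no data on this. At stake is the chance of detecting a real gain in days at home, ICU or hospital stay, or intubation time, in a trial of 214 patients.

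**Working it through.** **1. The plan's own figure.** Section 4.1 gives a power statement for delirium only. With the unpooled two-proportion formula:

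n = (1.96 + 0.842)² × (0.35 × 0.65 + 0.175 × 0.825) / 0.175² = 95.3, so 96 per group.

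96 / 0.90 = 106.7, so 107 per group and 214 in total. The figures reproduce. They do not depend on this point, and no power is stated for the endpoints discussed here. The checks below use 2 × 96 = 192 analysed patients.

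**2. Inputs not in the protocol (assumptions).** Site share of outcome variance ρ: 0% to 30%. Number of equal-sized sites: 2, 3 or 4. Blocks of 4 or 6. Treatment shift: 0.415 within-site SD, chosen so that the stratified test has about 80% power.

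**3. Normal approximation.** The plain test uses the total SD, but the contrast varies only with the within-site SD, so the effective critical value is 1.96 / √(1 − ρ).

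- Type I error = 2 × [1 − Φ(1.96 / √(1 − ρ))]
- Power = Φ(2.802 − 1.96 / √(1 − ρ)), where 2.802 corresponds to 80% power at ρ = 0

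For ρ = 20%: 1.96 / √0.8 = 2.191. Type I error is 2.8%, and power is Φ(0.610) = 72.9%. The other values of ρ give:

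- 5%: type I error 4.4%, power 78.5%
- 10%: 3.9%, 76.9%
- 30%: 1.9%, 67.7%

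**4. Simulation.** 4,000 trials per setting, two-sided 5%. The comparator is van Elteren's test: T = Σ Wₛ / (nₛ + 1), with variance Σ Vₛ / (nₛ + 1)². Here Wₛ is the centred rank sum of the training arm in site s, Vₛ its variance, and nₛ the number of patients at the site. Ranges run over 2, 3 and 4 sites.

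| Site share | Type I, plain | Type I, stratified | Power, plain | Power, stratified | Points lost |
|---|---|---|---|---|---|
| 0% | 4.6-5.2% | 4.6-5.2% | 78.7-79.7% | 78.1-79.4% | none |
| 5% | 4.1-4.8% | 4.9-5.4% | 77.5-78.1% | 78.4-79.4% | 0.4-1.5 |
| 10% | 3.7-3.9% | 4.4-5.0% | 76.2-77.1% | 79.0-80.3% | 2.8-3.2 |
| 20% | 2.9-3.0% | 4.9-5.3% | 69.9-71.9% | 77.4-79.5% | 7.5-8.0 |
| 30% | 1.8-2.4% | 4.6-5.5% | 66.0-66.9% | 79.5-80.8% | 12.8-14.0 |

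A skewed version in whole days with ties (3 sites) agrees. At 10% the plain test has type I error 3.9% and power 76% against 79%; at 20%, 3.1% and 71% against 79%.

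**5. A simulated DAOH30.** Assumed: log-normal stay with median 11 days, 3% of values set to 0 for death, shift 0.38 SD on log stay, 3 or 6 sites. Plain against stratified power:

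- 0%: 67% against 66-67%
- 5%: 66-67% against 68%
- 10%: 66-67% against 69-71%
- 20%: 67-70% against 75-77%
- 30%: 69% against 81-82%

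The plain test's type I error was 4.2-4.4% at 10%, 3.5-3.6% at 20% and 2.3% at 30%. A further run with 3 or 6 sites gave about 2.7% at 30%. In one set of runs the stratified test's error rate reached 6.0%. The simulation standard error is √(0.05 × 0.95 / 4000) = 0.34 points, and other runs of the stratified test gave 4.3-5.7%, so near 5% is the fair description.

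**The case against.** The best defence is that the planned test is valid. It does not raise the false-positive rate or bias a result, and the endpoints are secondary with no power claim. All of that stands, so this is a point about efficiency only.

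Four stronger readings are tempting, and the documents do not support them.

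- **That the test is in fact too conservative.** The protocol says only that centre effects may exist. At a 0% site share nothing is lost, and at 5% the loss is 1-2 points. The 12-14 points belong to an assumed 30%, for which the protocol gives no evidence.
- **That these endpoints will certainly go to Mann-Whitney.** The choice depends on the observed distribution. DAOH30 is bounded, with deaths set to 0, and the others are durations, so a non-Gaussian shape is likely but not stated. The alternative t test is equally unstratified, so the point survives either way.
- **That site is otherwise ignored.** Besides the logistic model there is the post-hoc analysis with study site. It names no endpoint or model, so it does not replace a prespecified test, but it should be acknowledged.
- **That aim 5 cannot be met because no difference in days with an interval is named.** Which estimate accompanies a secondary rank test is a detail that a separate statistical analysis plan may supply. It is not a fault of this protocol.

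**Conclusion.** The point holds in conditional form. The protocol stratifies by site, allows for centre effects, and then names tests for its day-count and duration endpoints that ignore site. If site affects those outcomes, the plain test is valid but conservative.

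Taking the different set-ups together, site shares of 0% / 5% / 10% / 20% / 30% give type I error of about 5% / 4.5% / 4% / 3-3.5% / 2-2.7%. The corresponding power loss is about 0 / 1-2 / 3-4 / 7-8 / 12-14 points. These figures rest on 192 analysed patients, equal-sized sites and an assumed site share. The direction does not depend on the exact values; the size does. Nothing here bears on the primary chi-square test.

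**What to change.** In section 4.2.5, for DAOH30, ICU stay, postoperative hospital stay and intubation time, replace the Mann-Whitney test by the site-stratified Wilcoxon (van Elteren) test. Where a t test would apply, use a linear model with site as a factor. A site-stratified difference in days with a 95% CI (Hodges-Lehmann, or a difference in means with bootstrap resampling within site) may be reported alongside.

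The cost is one sentence. It needs no new data and no more patients, and the test can be run in R, which the protocol already names. If sites turn out not to differ, almost nothing is lost: at a 0% share the simulated powers of the two tests differed by at most 0.6 points.
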